**Fig. 1 Fig1:**
[figure not shown]
Clinical timeline of the trial. Participants will complete assessment sessions fortnightly over the 8-week RCT period. “R” circles represent 1:1 random assignment of participants within each study stratum

The principal investigator (PI) and trial psychiatrist are aware which study participants are receiving celecoxib and which participants are receiving placebo, so that the dose of vortioxetine can be determined. An approximately twofold increase in vortioxetine plasma concentration has been observed following co-administration of bupropion, a strong CYP2D6 inhibitor [43]. When bupropion was added to vortioxetine 10 mg daily at steady state, a higher incidence of adverse events was observed than when vortioxetine was added to bupropion at steady state. This may be explained by pharmacodynamics or combined pharmacodynamic/pharmacokinetic effects following CYP2D6 inhibition with bupropion, which seem to be more pronounced when the inhibition is initiated when vortioxetine is in steady state than before vortioxetine is administered [43]. In the study where bupropion was added to vortioxetine, increased incidences of nausea, headache and vomiting were noted [43]. As celecoxib is also a strong inhibitor of CYP2D6, individuals receiving celecoxib start at a lower dose of vortioxetine, 5 mg daily, and are restricted to a maximum dose of 10 mg daily for the duration of co-administration. This is consistent with guidelines recommending the dose of vortioxetine be reduced by half if a strong CYP2D6 inhibitor is co-administered (Trintellix Product Monograph. Page 1 of 44, Lundbeck).

Furthermore, dosage of vortioxetine will vary to a small extent between participants even in the same strata, treatment group and time point. This is due to differences in CYP2D6 metabolic functionality in the general population related to common genetic variants [44]. Unfortunately, testing for genetic markers of CYP2D6 dysfunction at baseline, or plasma concentration of vortioxetine in all participants at all necessary time points, is beyond the scope of this study. Nevertheless, we account for this in two ways. First, for the safety and comfort of participants, each person will be started on a low dose and only increase if and when acceptable tolerability is demonstrated, as measured by a low number and mild severity of side effects reported to trial researchers on an in-house side effects questionnaire. The possible doses by strata and treatment group are given in Fig. 2. We are also able to assume, using this method, that the plasma concentration is comparable between all participants throughout the trial [44]. Additionally, the variable of dose differences will be factored into statistical analysis by noting the cumulative total dose of vortioxetine per participant over the entire study.

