According to stratified recruitment into the two treatment strata and the random allocation into two treatment groups, participants in both the ‘Depression with inflammation’ and ‘Depression without inflammation’ stratum receive celecoxib 400 mg daily or placebo. The starting dose of vortioxetine in both study strata is vortioxetine 5 mg daily for those receiving celecoxib, due to possible drug–drug interactions, and vortioxetine 10 mg daily for those receiving placebo. Two weeks after commencement of treatment, participants receiving vortioxetine 5 mg daily and 10 mg daily are provided the opportunity to increase to vortioxetine 10 mg or 20 mg daily, respectively, following an assessment by a research clinician (Fig. 2). The decision to increase the dose or to leave it the same is made by the trial psychiatrist after review of the change in depressive symptoms from baseline according to the MADRS and the presence and severity of side effects, rated by a blinded researcher. The dose of vortioxetine is increased only if the side effects experienced are easily manageable and the participants have not achieved recovery (MADRS score < 7). In study participants reporting symptoms consistent with an excessive plasma concentration of vortioxetine, the trial psychiatrist will reduce the dose of vortioxetine without informing the participant or blinded researchers administering scales. After six weeks of treatment, celecoxib and placebo are ceased, but the antidepressant vortioxetine is continued for at least two weeks. After the completion of the RCT phase, study participants are given the opportunity to continue taking vortioxetine into the post-RCT study phase for up to six months. Following an assessment by a research clinician, study participants who had been taking vortioxetine 5 mg or 10 mg daily during the RCT due to celecoxib co-administration are given the opportunity to increase to vortioxetine 10 mg and 20 mg daily, respectively; otherwise vortioxetine is continued in the post-RCT phase at the same dose as for the RCT phase.

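### Vortioxetine dose is to be factored into the analysis through a whole-study cumulative total, a post-randomisation variable that would bias the celecoxib comparison if adjusted for

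*Protocol article*

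**What the plan says.** Recruitment and study design acknowledges that vortioxetine dosage will differ between participants and offers two ways of dealing with it. One is tolerability-guided dosing, from which it assumes "that the plasma concentration is comparable between all participants throughout the trial". The other is analytic: "dose differences will be factored into statistical analysis by noting the cumulative total dose of vortioxetine per participant over the entire study".

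The dosing text makes dose depend on arm. In the same section, "individuals receiving celecoxib start at a lower dose of vortioxetine, 5 mg daily, and are restricted to a maximum dose of 10 mg daily" during co-administration, because of a presumed interaction. Study schedule gives "vortioxetine 10 mg daily for those receiving placebo" as the other starting dose. At two weeks the arms are "provided the opportunity to increase to vortioxetine 10 mg or 20 mg daily, respectively, following an assessment by a research clinician".

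Study schedule also makes dose depend on the course of illness. The trial psychiatrist, who knows the allocation, decides "after review of the change in depressive symptoms from baseline according to the MADRS and the presence and severity of side effects". Further, "The dose of vortioxetine is increased only if the side effects experienced are easily manageable and the participants have not achieved recovery". Doses may also be lowered for side effects.

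The primary time point is week 6. Celecoxib or placebo then stops, vortioxetine continues for at least two weeks, and an optional six-month phase follows in which former celecoxib participants may double their dose. Results analysis names treatment, baseline CRP and CRP stratum for the primary model. It names no dose variable.

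**The concern.** A covariate in a randomised comparison should be fixed before randomisation. Cumulative vortioxetine dose has three features that disqualify it.

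- It is a consequence of arm, because the two arms have different dosing rules.
- It is partly a consequence of early MADRS and tolerability, so it carries information about the outcome.
- Over the entire study it includes dosing after week 6, which the week-6 result can itself influence through the choice to continue or to increase.

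Conditioning on such a variable breaks the protection of randomisation. It also cuts across the article's own reasoning. The dose is halved under celecoxib so that exposure is comparable; equalising nominal milligrams in a model would then compare the arms at unequal exposure.

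The silence of Results analysis adds a second risk. With one section promising to account for dose and the other omitting it, dose-adjusted and unadjusted results could both be presented as planned.

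**Working it through.** **Plan's own figure.** The article gives no figure for cumulative dose or for the effect of adjusting for it. Its sample-size statement does not bear on this point.

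**Inputs from the article.** Celecoxib arm 5 mg daily, from week 2 up to 10 mg. Placebo arm 10 mg daily, from week 2 up to 20 mg. Endpoint at week 6 (14 + 28 days). Two further weeks (14 days). Optional six months (taken as 182 days). Allocation 50 v 50 within a stratum.

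**Assumptions (not in the article).** The shares up-titrated, reduced, continuing after the RCT phase, and doubling after it.

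**1. Dose to week 6, no reductions**

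- Celecoxib: 14×5 + 28×5 = 210 mg, or 14×5 + 28×10 = 350 mg
- Placebo: 14×10 + 28×10 = 420 mg, or 14×10 + 28×20 = 700 mg

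The ranges do not overlap. To week 8 with no further change they are 280–490 mg v 560–980 mg, again without overlap.

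**2. Dose over the whole study, full continuation**

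- Celecoxib: lowest 238×5 = 1190 mg; highest (increased at week 2, doubled after the RCT phase) 70 + 280 + 140 + 182×20 = 4130 mg
- Placebo: lowest 238×10 = 2380 mg; highest 140 + 560 + 280 + 182×20 = 4620 mg

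The ranges overlap widely, because the six optional months dominate the total.

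**3. Collinearity with arm.** VIF = 1/(1 − R²), where R² is the share of dose variance explained by arm, and the SE is multiplied by √VIF. For six-week dose with half up-titrated in each arm:

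- arm means 280 and 560 mg; between-arm variance (280/2)² = 19,600
- within-arm variance 0.25×(140² + 280²)/2 = 12,250
- R² = 19,600/31,850 = 0.615; VIF = 2.6; SE ×1.6

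| Dose used | Assumptions | VIF | SE multiplied by |
|---|---|---|---|
| To week 6 | 10–90% up-titrated, no reductions | 2.5–7.5 | 1.6–2.7 |
| To week 6 | same, 10% reduced | 2.1–3.1 | 1.5–1.8 |
| Whole study | 50–90% up-titrated, 80–100% continue, at least half of former celecoxib participants double | 1.02–1.62 | 1.0–1.3 |
| Whole study | all continue, none double, 90% up-titrated | 5.3 | 2.3 |

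**4. Bias.** Assume up-titration follows week-2 severity, which correlates 0.6 with week-6 severity; dose itself has no effect on outcome; the true benefit is 0.50 SD; half are up-titrated.

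- Within an arm, those up-titrated end worse by 0.6 × 2 × 0.798 = 0.957 SD (0.798 is the mean of the upper half of a standard normal).
- Fitted within-arm slope: 0.957×(140 + 280)/(140² + 280²) = 402/98,000 = 0.0041 SD worse per mg.
- The arms differ by 280 mg, so the model moves the comparison against celecoxib by 280×0.0041 = 1.15 SD.
- Adjusted estimate: 0.50 − 1.15 = −0.65 SD.

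Simulation with 100 per stratum under similar assumptions gave:

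| Analysis | Estimate when the truth is 0.50 SD | False rejection when the truth is 0 |
|---|---|---|
| No dose term | 0.50 | about 5% |
| Whole-study dose (80% continue, doubling tied to a poor week-6 score) | 0.21 | about 16% |
| Six-week dose | −0.70 to −0.87 | about 98% |

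These figures show what can happen under the stated assumptions. They do not forecast this trial.

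**5. The plasma statement.** Comparability is assumed for the whole trial. The lower ceiling is tied to co-administration ("restricted to a maximum dose of 10 mg daily for the duration of co-administration"), celecoxib stops at week 6, and the prose describes that arm's later increase only after the RCT phase. On the article's own interaction reasoning, weeks 6 to 8 are not covered by the assumption. The dosing figure (Fig. 2) is not available here.

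**The case against.** The strongest reply is that no dose-adjusted model is actually specified. The sentence speaks of noting the dose and names no covariate or endpoint, and Results analysis has no dose term. How dose is used could be left to a fuller document. The remark also arises from small variation within the same arm. If dose were centred within arm, it would not be collinear with arm and would leave the arm difference essentially unchanged.

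Much of this stands. A reader might infer that the primary model adjusts for dose; the article does not say so. It does, however, present the cumulative total as one of two ways of accounting for dose differences, and covariate adjustment is the natural reading. Nothing limits its use to a within-arm or descriptive one.

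Three stronger readings should be resisted.

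- Dose nearly duplicates arm and would ruin precision. This fits the six- or eight-week dose. It does not generally fit the whole-study total that the article names.
- The variance inflation can be turned into a loss of power. That presumes the adjusted coefficient still estimates the true effect, which fails when titration follows outcome.
- Non-responders are the ones up-titrated. The rule bars an increase only for recovery (MADRS below 7) or side effects that are not easily managed. With entry at MADRS 26 or more, many responders could be increased too. MADRS change is reviewed, but no non-response rule exists.

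**Conclusion.** The point holds in a limited form. The article commits to factoring in a dose total that is determined by arm, by on-treatment MADRS and tolerability, and by dosing after the endpoint, while its analysis section has no such term. If that total entered the model for the celecoxib effect, the comparison would be biased.

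The direction of the argument rests on the article's text alone. The size does not: it depends on titration, reduction, continuation and doubling rates that are not given, and on how closely dose decisions follow MADRS. Bias is the main problem. Imprecision is secondary and applies mainly if dose is cut off at week 6 or 8.

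A reader might also infer that dosing in weeks 6 to 8 contradicts the plasma assumption outright. Without the dosing figure, the documents support only a request to reconcile the passages.

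**What to change.** - In Recruitment and study design and in Results analysis, state that vortioxetine dose does not enter the primary model or any other efficacy model.
- Analyse by randomised arm, and word the conclusion as a comparison of regimens: celecoxib with its vortioxetine dosing rule v placebo with its dosing rule.
- Report cumulative dose to week 6 by arm descriptively. Label any dose analysis exploratory and limit it to dose before week 6.
- Reconcile the statement on comparable plasma concentration throughout the trial with the passages on stopping celecoxib at week 6 and on the later dose change.

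The cost is wording only; no data collection or sample size changes. The downside is that the conclusion concerns the regimen, not celecoxib at identical vortioxetine exposure. Adjusting for nominal dose would not supply that contrast either.

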**Fig. 2 Fig2:**
[figure not shown]
Diagram stating the possible dosages of vortioxetine (antidepressant medication) and celecoxib (anti-inflammatory medication) within each group for all the periods of the trial

To promote participant retention, study participants are encouraged to contact the study team if any side effects cause them serious concern between appointments, allowing for the dosage of vortioxetine to be lowered if possible, in the hope of reducing the likelihood of early withdrawal from the study. In the case of early withdrawal from the study, all endpoint scales and blood collection will be conducted immediately for later analysis.

### Double-blinding

The trial psychiatrist and the study PI do not administer the MADRS or any of the functional rating scales, as they are aware of both the dose of vortioxetine and whether a participant is receiving celecoxib or placebo. While the PI is aware which study participants are receiving celecoxib and which participants are receiving placebo, the study rater and participants remain fully blinded during the entire trial. Celecoxib has been encapsulated to have the same appearance as placebo; celecoxib and placebo have been packaged in the same way. A randomisation list has been created by the Royal Adelaide Hospital pharmacy and provided to the trial psychiatrist. The dosage of vortioxetine is not marked specifically on the package provided to participants in order to maintain blinding of participants as well as researchers administering the scales who may see the boxes.

### Study sample size

Given a power of 0.95, and an alpha error of 0.05, the study sample size required to detect a change in MADRS of an effect size of 0.25 between baseline and week 6 would be 50 study participants in each of the four groups. This would be a total of 200 study participants (100 participants in the ‘Depression with inflammation’ stratum and 100 study participants in the ‘Depression without inflammation’ stratum; 50 participants in each treatment group, respectively).

We have found in our internal analyses that around 40–50% of individuals have a CRP level of > 3 mg/L, so we expect to be able to recruit 100 participants to the ‘Depression with inflammation’ stratum and 100 participants to the ‘Depression without inflammation’ stratum. The proposed study duration is two years, which will allow time to recruit the required number of study participants.

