We therefore propose that testing CRP levels in a blood test before the commencement of treatment in patients with MDD will give clinicians an informative biomarker at hand to guide the selection of effective antidepressant treatment. CRP was chosen as the informative inflammatory marker not only because it can predict improvement in depressive symptoms following anti-inflammatory treatment [34] but also because CRP detection in the blood can be routinely done in pathology services and hence shows potentially high clinical utility. Vortioxetine was chosen as the antidepressant medication; since it has a recently obtained Therapeutic Goods Administration (TGA) indication in Australia for the treatment of MDD, it is more likely to be useful in severe depression [39] and is likely to be useful in enhancing the remittance of cognitive symptoms of depression [40]. It will be novel to investigate its potential immune-modulatory effects in secondary analyses. Celecoxib was chosen as the trial anti-inflammatory medication because of its ability to increase the efficacy of antidepressant medication when used as an augmentation strategy [41, 42]. This is a first adequately powered, RCT that prospectively tests the efficacy of an antidepressant plus adjunctive anti-inflammatory treatment based on baseline CRP levels in MDD. This approach will inform real-world treatment of depression based on a widely available blood test.

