### Recruitment and study design

A total of 200 patients with MDD will be included in the study. Recruitment and treatment take place in the wider Central Adelaide Local Health Network (CALHN), with all participant appointments being held in the Clinical Research Facility in the Health and Medical Sciences Building, Discipline of Psychiatry, University of Adelaide. In addition to this, and to ensure that required numbers of study participants are recruited, people from the general population who meet the inclusion criteria are able to engage with the proposed study, as it is made available through advertisement. Participants are free to withdraw from the study at any time.

The study is designed as a parallel group RCT with a superiority framework, investigating 200 participants with MDD over six weeks in the primary phase followed by a six-month post-RCT follow-up period (Fig. 1). The study proposes to measure the inflammatory marker CRP before the commencement of treatment. Following CRP measurement, study participants are then assigned into one of two study strata based on CRP levels. The first of these study strata is made up of 100 individuals with CRP levels > 3 mg/L (the ‘Depression with inflammation’ stratum) and the second study stratum is an active control, made up of 100 individuals with CRP levels ≤ 3 mg/L (the ‘Depression without inflammation’ stratum). In each stratum, participants are randomly allocated in a 1:1 ratio to augmentation of vortioxetine antidepressant treatment with either celecoxib or placebo. Following six weeks of concomitant administration of celecoxib or placebo with vortioxetine, the celecoxib or placebo is then stopped and the participants are treated with vortioxetine only for an additional two weeks. This allows the opportunity to assess the efficacy of taking vortioxetine alone. While the primary time point is the six weeks in which we compare vortioxetine with augmentation against vortioxetine without augmentation, following the RCT phase, all participants have the opportunity to continue on vortioxetine without celecoxib or placebo for another six months during a post-RCT observational study period.

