## Medications

### Celecoxib

Celecoxib, a cyclooxygenase 2 inhibitor, is a NSAID that has previously been used as an adjunct to antidepressant medication in the treatment of MDD in four trials, with three of these trials exploring six weeks of treatment at 400 mg daily [45–47] and one trial of eight weeks at 200 mg daily [48]. All four of these trials suggested improved antidepressant treatment effects for celecoxib add-on treatment, compared to antidepressants plus placebo. Recent meta-analyses associated celecoxib with an increased efficacy of antidepressant therapy [41]. In particular, augmentation of antidepressant medication with celecoxib showed an improved antidepressant effect by a standard mean difference (SMD) of 0.82 (95% confidence interval [CI]: 0.46–1.17) and without heterogeneity between the studies (I^2^ = 0%) [41]. Furthermore, remission of depression was improved by an odds ratio (OR) of 7.89 (95% CI: 2.94–21.17) and treatment response by an OR of 6.59 (95% CI: 2.24–19.42) by this 6–8-week add-on treatment hence the choice of celecoxib 400 mg for our study. Finally, one trial included peripheral blood tests and found that higher levels of the pro-inflammatory marker IL-6 predicted better antidepressant response to the celecoxib add-on [45]. In the present study, celecoxib 400 mg or placebo is given daily to all the participants at a constant dosage from baseline to week 6.

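### The stated 95% power at an effect size of 0.25 does not hold for the 50 v 50 primary contrast on the usual readings: about 24% if 0.25 is an SMD, about 70% if it is Cohen's f

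*Protocol article*

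**What the plan says.** The section on study sample size opens with "Given a power of 0.95, and an alpha error of 0.05" and continues that the number "required to detect a change in MADRS of an effect size of 0.25 between baseline and week 6 would be 50 study participants" per group. It thus arrives at 200 in total, 100 per CRP stratum. It does not say whether 0.25 is an SMD, a Cohen's f or a paired change. It gives no SD or MADRS points, no test, no sidedness and no contrast.

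Under Objectives, the primary hypothesis is a larger benefit of combined treatment than of antidepressant alone in people with CRP > 3 mg/L. Recruitment and study design fixes 100 people in each stratum, where "participants are randomly allocated in a 1:1 ratio to augmentation of vortioxetine antidepressant treatment with either celecoxib or placebo". The hypothesis is therefore tested on 50 v 50.

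Three other statements bear on the point:

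- The Background describes the trial in these words: "This is a first adequately powered, RCT that prospectively tests the efficacy".
- The Celecoxib section cites an "improved antidepressant effect by a standard mean difference (SMD) of 0.82" (95% CI 0.46 to 1.17). The sample size section does not use it.
- The secondary objectives and Results analysis concede low power for the stratum-by-treatment interaction. Neither qualifies the power for the within-stratum comparison.

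**The concern.** The sentence is a complete power claim: power, alpha, effect size and number per group. It can therefore be checked, and a reader will apply it to the primary hypothesis. The only other standardised treatment effect in the article is an SMD, so 0.25 will naturally be read on that scale. Fifty per arm is far too few to give 95% power for an SMD of 0.25.

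What is at stake is how a null result would be read. The Discussion envisages recommending augmentation only for patients with raised inflammation if the effect is larger in them. If the inflamed stratum shows no difference, the printed power would suggest that even a small effect has been all but excluded. On the SMD reading, a true effect of 0.25 would be missed about three times in four.

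**Working it through.** **Inputs.** Power 0.95, alpha 0.05, effect size 0.25 and 50 in each of four groups (Study sample size); 1:1 allocation within stratum (Recruitment and study design); primary hypothesis in the CRP > 3 mg/L stratum (Objectives). Sidedness is not stated. Two-sided is assumed, and one-sided results are also shown.

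**Step 1: try to reproduce 50 per group.** For two means, n per arm = 2(z₀.₉₇₅ + z₀.₉₅)²/d², with (1.960 + 1.645)² ≈ 13.0.

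| Reading of 0.25 | Needed for 95% power | Power at the planned size |
|---|---|---|
| SMD, two arms | 2 × 13.0/0.0625 ≈ 416 per arm (417 by noncentral t) | 23.6% at 50 v 50 |
| Cohen's f, two arms (d = 2f = 0.5) | 2 × 13.0/0.25 ≈ 104 per arm | 69.7% at 50 v 50 |
| f, four-group omnibus F test | 279 in total | 84.8% at N = 200 |
| f, one-degree-of-freedom treatment effect over all groups | 210 in total | 94.0% at N = 200 |
| Paired change of 0.25 SD, no comparator | not solved separately | 41% at n = 50; 94.0% at n = 200 |

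None of these returns 50 per group. The nearest two reach 94.0%, and both use all 200 participants. Their noncentrality is the same: 0.25 × √200 = 3.54, and Φ(3.54 − 1.96) = Φ(1.58) ≈ 0.94.

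**Step 2: power for the primary contrast.** Power ≈ Φ(d√(n/2) − 1.96). With n = 50, √(n/2) = 5.

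- d = 0.25: Φ(1.25 − 1.96) = Φ(−0.71) = 23.9%; noncentral t gives 23.6%.
- d = 0.46: Φ(2.30 − 1.96) = Φ(0.34) = 63.3%; noncentral t gives 62.5%.
- d = 0.50: Φ(2.50 − 1.96) = Φ(0.54) = 70.5%; noncentral t gives 69.7%.
- d = 0.82: Φ(4.10 − 1.96) = Φ(2.14) = 98.4%; noncentral t gives 98.2%.

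One-sided testing gives about 34% at d = 0.25 and 80% at d = 0.5.

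**Step 3: detectable effect at 50 per arm.** The normal approximation gives (1.960 + 0.842) × √(2/50) = 2.802 × 0.2 = 0.56 for 80% power, and 3.605 × 0.2 = 0.72 for 95%. The noncentral t gives 0.566 and 0.728. With 40 per arm (20% drop-out, an assumption) it gives 0.634 and 0.816.

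**Step 4: baseline adjustment.** The article gives no correlation between baseline and week 6, so a range is shown. Adjustment divides the SD by 1/√(1 − r²), that is, multiplies it by √(1 − r²).

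| Assumed r | Power, SMD 0.25 | Power, f = 0.25 (SMD 0.5) |
|---|---|---|
| 0.3 | 26% | 75% |
| 0.5 | 30% | 82% |
| 0.7 | 42% | 94% |

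Reaching 95% would need r of about 0.94 on the SMD reading or 0.725 on the f reading.

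**Step 5: a repeated-measures reading.** Suppose 0.25 is Cohen's f on the cell means of a group-by-time interaction with two groups and two times. Each cell mean then departs by 0.25σ, so the arms differ in change by 4 × 0.25σ = 1.0σ. The SD of change is σ√(2(1 − ρ)).

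- ρ = 0: SMD on change = 1/√2 = 0.71; power at 50 v 50 is 93.8%, and 106 in total are needed for 95%.
- ρ = 0.5: SMD on change = 1/1 = 1.0; power is over 99%, and only 54 in total are needed.

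This reading can give high power at 50 v 50, but only by assuming a large treatment effect.

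**The case against.** The strongest reply is that the calculation may belong to the whole sample. The main model in Results analysis has treatment as the fixed factor and controls for stratum, which is a treatment effect pooled over 100 v 100. The primary objective, unlike the hypothesis, is not restricted to a stratum. With 0.25 read as f, that contrast has 94.0% power, one point short of the stated figure. This stands as the likeliest origin of the number. It locates the fault as a whole-sample calculation set beside a stratum-specific hypothesis. It does not rescue the claim for that hypothesis, and on the SMD reading the pooled contrast has only 42% power.

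Three stronger readings are tempting, and the document does not support them:

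- A reader might infer that no interpretation of 0.25 gives 95% power at 50 v 50. Step 5 shows that a repeated-measures f comes close or exceeds it. That metric is unstated, and an SMD of 0.7 to 1.0 should not be printed as an unlabelled 0.25.
- A reader might infer from the 40–50% prevalence of raised CRP that 200 participants would yield only 80 in the inflamed stratum. The Methods fix 100 per stratum, and the prevalence is offered to show that recruitment is feasible.
- A reader might infer that the trial is underpowered altogether. At the cited SMD of 0.82 it has 98% power for 50 v 50, so the Background claim needs qualifying, not deleting.

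Drop-out is a lesser matter. A journal article may leave the allowance to the full protocol, and the plan collects endpoint scales at withdrawal and analyses all available data. The 20% used above is only an illustration.

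**Conclusion.** The power statement is wrong as written for the hypothesis the trial names. For celecoxib v placebo within CRP > 3 mg/L, power is about 24% if 0.25 is an SMD and about 70% if it is Cohen's f, against a stated 95%. Both figures are conditional on the undefined metric and assume a two-sided 5% test, 50 analysed per arm and no baseline adjustment. Plausible adjustment leaves the SMD reading far below 95%.

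The design is sound for large effects: 95% power from an SMD of about 0.73 upwards. That includes the meta-analytic estimate the article cites, but not its lower confidence limit of 0.46, where power is 62%.

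**What to change.** Keep N = 200. In Study sample size, name the effect-size metric, the test, its sidedness and the contrast, and replace the power sentence with wording such as:

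> In the stratum with CRP > 3 mg/L, 50 participants per arm give 80% power for an SMD of 0.57 and 95% power for an SMD of 0.73 (two-sided 5%, before drop-out and without baseline adjustment). Power for an SMD of 0.25 is about 24%. If 20% drop out (assumed), the detectable SMDs are 0.63 and 0.82.

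If the calculation was meant for the treatment effect pooled over strata, or for a repeated-measures f, say so, give the equivalent SMD, and still report the within-stratum figures. In the Background, qualify the claim of adequate power as holding for within-stratum effects of about 0.73 or more.

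The cost is wording only: no added participants and no change to design or analysis. The stated power becomes less favourable.
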